### Outcome measurements and follow-ups

In Table 2, criteria are listed in detail to distinguish the central vestibular system (CVS) compensation and peripheral vestibular system (PVS) restoration according to the following evidence:
SOT is a measurement for dynamic and static posturography, which may figure out the different roles of the somatosensory, visual, and vestibular systems. The vestibular scores in SOT will help us to distinguish peripheral function self-restoration from CVS compensation.The caloric test has been used to evaluate the lateral semicircular canal function with a good sensitivity [11]. In the caloric test, unilateral weakness (UW), directional preponderance (DP), and spontaneous nystagmus (SpN) are three parameters to judge the different phases of central vestibular compensation. UW presents at all three phases of acute injury, static compensation, and dynamic compensation phase and DP presents at the acute injury phase and static compensation phase, while SpN only presents at the acute injury phase [12]. Meanwhile, the caloric test results of complete function restoration in PVS should be the same as those in normal individuals: absence of UW, DP, or SpN.vHIT can be employed for evaluating horizontal and vertical semicircular canals and has been taken as a specific indicator of peripheral vestibular function [13, 14]. The decreased gains and corrective saccades are signs of the corresponding semicircular canal dysfunction.cVEMP is a widely used measurement for assessing the saccular and inferior vestibular pathway functions, while oVEMP for evaluating the utricular and superior vestibular pathway functions [15]. Based on the integrity of neural pathways, we may reasonably assume that if the dysfunction of otolith organ and its afferent pathway has not recovered in our participants, the compensation effects of CVS will not bring a normal VEMP result [14, 16].

**Table 2 Tab2:** Difference in vestibular function tests between compensation of the central vestibular system and restoration of the peripheral vestibular system

	Compensation of CVS	Restoration of PVS
Subjective complaints	Normal	Normal
SOT	Abnormal	Normal
Caloric test	Static compensation: UW+ DP+ Dynamic compensation: UW+ DP−	UW− DP−
vHIT	Abnormal	Normal
cVEMP/oVEMP	Abnormal	Normal

*CVS* central vestibular system, *PVS* peripheral vestibular system, *UW* unilateral weakness, *DP* directional preponderance, *SpN* spontaneous nystagmus

Here come two possible patterns in vestibular dysfunction recovery of ISSNHL. The first pattern (pattern A) is that the patients undergo well central vestibular compensations with no recovery of PVS function. In this pattern, patients may show a quite normal ability of balance evaluated by subjective complaints, DHI or VAS-V; however, since the peripheral vestibular organs remain dysfunctional, vestibular test battery (i.e., SOT, caloric tests, vHIT, and VEMPs) will come out with abnormal results. The second possible pattern (pattern B) is that the PVS injuries are completely or partially restored in the patients. In this condition, not only the subjective complaints will disappear, but also the objective vestibular test results will get back to normal, or at least less abnormal.

#### Measurements

The methodology details of the following tests have been reported before [17].

##### SOT

The SOT in our study is performed with the Synapsys Posturography System (SPS, SYNAPSYS, Inc. Marseille, France). Six sensory test modes are performed with changing supports and visual conditions. The results are analyzed comprehensively to give a score for each sensory system (somatosensory, visual, and vestibular systems) and a composite score. Results are considered abnormal when the score is lower than the age-specific normative data.

##### Caloric test

We deliver the caloric test using the air caloric irrigator system of ICS AirCal (GN Otometrics, Taastrup, Denmark) and record eye movements using videonystagmography (VNG) of SYNAPSYS VNG Ulmer (SYNAPSYS, Inc. Marseille, France). Patients are placed in a supine position in a darkroom, with the head flexed at 30°. The temperature of the warm and cool air is 50 °C and 22 °C, respectively. The unilateral weakness (UW) and directional preponderance (DP) are used to quantify the difference between the caloric responses of the two ears. The abnormal caloric result is defined as an absolute value of UW% greater than 22% and/or an absolute value of DP greater than 27%.

##### vHIT

ICS Impulse system (GN Otometrics, Taastrup, Denmark) will be used for vHIT in this study. The examiner performs head impulses (150 to 200°/s peak head velocity) randomly in unpredictable timing and direction in the plane of each canal (the horizontal, anterior, and posterior semicircular canal), and at least 15 impulses for each side are acquired. The software analysis algorithm calculates the vestibular-ocular gain. Normal gain is defined as > 0.8 for the lateral canals and > 0.7 for the vertical canals. The pathological saccade is defined as refixation saccades categorized as either covert saccades (occurring during a head movement) or overt saccades (occurring after a head movement) [18]. The result of a semicircular canal will be considered abnormal when there are pathological saccades and the gain is out of normal range.

##### VEMP

The recording device of both cVEMP and oVEMP is the Bio-logic Navigator PRO (Natus Medical Inc., San Carlos, USA).

##### cVEMP

Patients are asked to lie in supine position on a bed, with head raised to 30 to 45° away from the bed during recording to ensure good muscle tone. Electrodes are placed as operation manual. Air-conducted sound with 500-Hz short tone bursts (2 ms rise/fall time and 2 ms plateau time) are presented through insert headphones as stimuli. The starting stimulus intensity is 95 dB nHL and decreases by 5 dB nHL each time until the meaningful wave is undetectable. The lowest intensity with a characteristic waveform is defined as threshold. The result will be considered abnormal if one of the following conditions is met: (1) the amplitude asymmetry ratio (AR) is more than 37%; (2) the cVEMP meaningful waveform (where the waveforms with positive-negative-positive peak, P1-N1-P2, could be recognized and well repeatable) is absent at 95-dB nHL stimulus or the threshold is out of range compared with age-specific normative data; (3) delayed response: the cVEMP threshold shift is out of the range: P1 range 15.66 ± 7.22; N1 range 23.42 ± 5.18 (the mean of normal range ± 2 × SD) [19–22].

##### oVEMP

The recording device, software, and stimuli are the same as those in cVEMP. The patients remain lying supine and are asked to look upward (approximately 30° above the horizontal plane) during recording. Electrodes are placed as reported in previous studies [17]. The recording procedure is the same as that in cVEMP, and the lowest intensity with a characteristic waveform is defined as threshold. We define the abnormal result of oVEMP as (1) absence of meaningful waveform (where the waveforms with negative-positive peak, N1-P1, could be recognized and well repeatable); (2) the threshold out of range compared with age-specific normative data; and (3) amplitude asymmetry ratio (AR) ≥ 40% [19, 20].

All examinations will be performed by trained physicians skilled at neuro-otological tests.

##### DHI and VAS

The dizziness handicap inventory (DHI) is a self-assessment questionnaire with 25 items, and the reliability of the Chinese version has been verified [23–26]. The 25 items can be divided into 3 subscales: physical, emotional, and functional aspects, and the total scores range from 0 to 100. The higher the score, the more severe the dizziness is in the patients.

Visual analogue scale is a universal psychometric scale evaluating subjective attitudes [27, 28]. When applied in vertigo or tinnitus (VAS-V or VAS-T), respondents specify their level of vertigoes or tinnitus by indicating a position along a continuous line between two endpoints without marked scale. A score from 0 to 10 will be made based on the length of the line. The higher the score, the more severe the symptom is.

#### Primary outcomes

To evaluate the recovery of vestibular function, we set the recovery rates of the whole battery of vestibular function tests (SOT/caloric test/vHIT/VEMPs) as the primary outcome, which is the proportion of patients whose abnormal results of vestibular function tests at baseline recover to normal at 4-/8-week follow-up:
$$ \mathrm{recover}\mathrm{y}\ \mathrm{rate}=\frac{\begin{array}{c}\mathrm{number}\ \mathrm{of}\ \mathrm{patients}\ \mathrm{recover}\ \mathrm{from}\ \mathrm{abnormal}\ \mathrm{result}\ \mathrm{at}\ \mathrm{baseline}\\ {}\ \mathrm{to}\ \mathrm{normal}\ \mathrm{at}\ 4-/8-\mathrm{week}\ \mathrm{follow}-\mathrm{up}\end{array}}{\mathrm{number}\ \mathrm{of}\ \mathrm{all}\ \mathrm{enrolment}\ \mathrm{participants}}\times 100\%. $$

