**Methods/design:**

A randomized, outcome-assessor- and analyst-blinded, controlled, clinical trial (RCT) will be carried out. Seventy-two patients with ISSNHL complaining of vestibular dysfunction appearing as vertigo or imbalance will be recruited and randomized into either oral or intratympanic glucocorticoid therapy group with a 1:1 allocation ratio. The primary outcomes will be vestibular function outcomes assessed by sensory organization test, caloric test, video head impulse test, cervical vestibular evoked myogenic potential, and ocular vestibular evoked myogenic potential; the secondary outcomes include self-reported vestibular dysfunction symptoms; dizziness-related handicap, visual analogue scale for vertigo and tinnitus; and pure tone audiometry. Assessments of primary outcomes will be performed at baseline and at 4 and 8 weeks post-randomization, while assessments of secondary outcomes will be performed at baseline and 1, 2, 4, and 8 weeks post-randomization.

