### Sample size and statistical methods

In our previous studies, we reported the poor indicator of the vestibular system lesion patterns in SSNHL and put forward that the incidence of vestibular dysfunction [30, 31]. However, we only found the existence of vestibular recovery in clinical case reports [16]. Due to lack of previous reported data on changes of vestibular function test results, this study sample size was calculated based on data from preliminary clinical practice in our hospital. Among patients who were diagnosed as ISSNHL and treated with oral prednisone, the recovery proportion of the vestibular function tests (measured by SOT, caloric test, or VEMPs) was 0.25, while the recovery proportion among those treated with intratympanic glucocorticoids was approximate 0.64. Using the program of G*Power 3.1 for Fisher’s exact test, we calculated a sample size of 30 per arm with 80% power at a two-tailed 5% level of significance [32]. To allow for 20% dropout, 36 participants per arm will be needed.

For the outcomes, categoric variables will be expressed as rates, while numerical variables as the mean ± SD. Baseline data will be compared between two groups with a chi-squared test for dichotomous samples and Student’s *t* test or Mann-Whitney *U* test for two independent samples where appropriate. For comparisons of recovery in 4 and 8 weeks from baseline, the recovery rates of vestibular function tests will be calculated by chi-squared tests, and logistic regression adjusts for potential confounders like age, initial PTA, the number of involved vestibular organs, MRI-IAC results, and other characteristics, while the numerical variables like UW of the caloric test, PTA, and scores in DHI, VAS-V, and VAS-T will be calculated by mixed-model with repeated measures analyses of variance (ANOVA), with group and time as fixed effects and subject as a random effect, controlling for the potential confounders. Between two intervention groups, the chi-squared test will be used to analyze the difference for dichotomous outcomes (e.g., recovery rates) and Student’s *t* test for two independent samples or Mann-Whitney *U* test where appropriate. A value of *p* < 0.05 of two-sided is considered statistically significant. We will calculate relative risk (RR) with corresponding 95% confidence intervals to compare dichotomous variables, and mean difference (MD) for continuous variables.

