An ITT analysis and a per-protocol analysis will be both performed at each outcome. For the missing data in ITT analyses, if there is any, multiple imputation methods will be used. Up-to-date versions of SPSS (SPSS, Chicago, IL, USA) will be used to conduct analyses. A statistician from the Medical College of Fudan University will perform the analyses. Not until the statistician complete the analysis, will he be unblinded to the group allocations and the study hypotheses. All data sent to the analyst will be anonymized, and the study groups will be coded as groups A and B.

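### The primary comparison is not fixed: neither the visit nor the rule for combining abnormal tests is stated, so the planned 5% level and 80% power are tied to no single defined test

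*Protocol article*

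**What the plan says.** The Primary outcomes section of the protocol article states: "we set the recovery rates of the whole battery of vestibular function tests (SOT/caloric test/vHIT/VEMPs) as the primary outcome". It defines this as a proportion of patients whose abnormal baseline results "recover to normal at 4-/8-week follow-up". One formula follows, with all enrolled participants in the denominator.

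The abstract (Methods/design) uses the plural and lists by test: "The primary outcomes will be vestibular function outcomes assessed by sensory organization test, caloric test, video head impulse test", followed by cVEMP and oVEMP.

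Sample size and statistical methods plans chi-squared tests and adjusted logistic regression for recovery at 4 and 8 weeks. It gives one threshold for everything: p < "0.05 of two-sided is considered statistically significant". It adds: "An ITT analysis and a per-protocol analysis will be both performed at each outcome".

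The sample size rests on one pair of rates. For oral prednisone, "the recovery proportion of the vestibular function tests (measured by SOT, caloric test, or VEMPs) was 0.25"; for the other arm, "the recovery proportion among those treated with intratympanic glucocorticoids was approximate 0.64". From these, using Fisher's exact test, "we calculated a sample size of 30 per arm with 80% power at a two-tailed 5% level of significance".

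Under Participants, eligibility requires an abnormal result on at least one vestibular test, so a patient may enter with anything from one to five abnormal tests.

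**The concern.** A confirmatory trial needs one comparison, or a declared family of comparisons, to which its error rate and power belong. Here three elements of that comparison are open or inconsistent.

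- **Visit.** Both weeks appear in the definition and in the formula, and neither is called primary.
- **Combination rule.** For a patient with, say, three abnormal tests at baseline, the text does not say whether recovery means all three normal or at least one normal.
- **Number of outcomes.** The Primary outcomes section describes a single outcome for the battery. The abstract describes several, one per test.

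The planning rates add a fourth gap. They come from SOT, caloric test or VEMPs, without vHIT and without a time point, whereas the primary battery includes vHIT.

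The hypothesis in the Background is that intratympanic treatment is superior on vestibular recovery. As written, that claim could be made from whichever visit, or whichever definition of recovery, reaches p < 0.05. The 5% used in the sample size would then not be the trial's error rate.

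**Working it through.** **1. The plan's own figure.** Inputs from Sample size and statistical methods: rates 0.25 and 0.64, Fisher's exact test, two-sided 5%, 80% power. Power is the sum, over all pairs of counts (i, j), of Bin(i; n, 0.25) × Bin(j; n, 0.64) wherever the Fisher p-value is at most 0.05.

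- n = 29 per arm: 79.5%
- n = 30 per arm: 81.9%

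The stated 30 per arm reproduces, so the arithmetic is sound.

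**2. One composite, two visits, each at 0.05.** If the visits were independent, the chance of at least one false positive would be 1 − 0.95² = 9.75%. They are the same patients, so the test statistics are correlated. The documents give no correlation, so a range is assumed and the bivariate normal is simulated (400,000 draws):

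| Assumed correlation | Any false positive |
|---|---|
| 0.5 | 9.0% |
| 0.7 | 8.3% |
| 0.8 | 7.8% |
| 0.9 | 7.1% |

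The null is symmetric, so about half of each figure is a false result in favour of intratympanic treatment (roughly 3.5–4.5%, against a nominal 2.5%).

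**3. Five separate tests, two visits (the reading the abstract allows).** Independent: 1 − 0.95¹⁰ = 40.1%. With an assumed correlation of 0.7 between visits, simulation gives about 34% for a between-test correlation of 0.2 and about 29% for 0.5. In favour of intratympanic only, the corresponding figures are about 18% and 14%, and 1 − 0.975¹⁰ = 22% under independence.

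**4. How far power depends on the combination rule.** The documents do not say whether 0.25 and 0.64 are per-test or per-patient rates. As an illustration, assume that they are per-test rates, that tests are independent within a patient, and that every patient has exactly k abnormal tests. The all-normal rule then compares 0.25ᵏ with 0.64ᵏ, and the any-normal rule compares 1 − 0.75ᵏ with 1 − 0.36ᵏ. Fisher power at 30 per arm:

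| k | All normal: rates | Power | Any normal: rates | Power |
|---|---|---|---|---|
| 2 | 0.063 vs 0.410 | 87% | 0.438 vs 0.870 | 93% |
| 3 | 0.016 vs 0.262 | 71% | 0.578 vs 0.953 | 93% |
| 4 | 0.004 vs 0.168 | 36% | 0.684 vs 0.983 | 86% |

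The same planning rates and sample size therefore give anything from 36% to 93%, depending on a rule that the protocol does not state.

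**The case against.** The best defence is that the protocol does intend one composite. Primary outcomes uses the singular, speaks of the whole battery, defines a proportion of patients and gives one patient-count formula; the sample size uses one pair of rates. This stands to the following extent: no section says that each of the five tests is judged separately at 0.05. A reader might infer from the abstract that ten tests are planned and that the error rate is 40%. The documents allow that reading but do not establish it, and the 40% also needs independence and counts results in either direction.

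Three further inferences are not supported.

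- **ITT and per-protocol as a doubling of the tests.** They are two highly correlated views of the same comparison, and reporting both is ordinary practice. The only point is that neither is called primary, a detail that an analysis plan may supply.
- **Planning on a different battery.** SOT, caloric test and VEMPs match; only vHIT is absent. No figure in the document shows that adding it would change 0.25 or 0.64.
- **An underpowered trial.** The stated 30 per arm reproduces. The table in step 4 is hypothetical, and four of its six values exceed 80%.

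It could also be said that the choice of visit and the multiplicity rule belong in an analysis plan that is not shown. That does not dispose of the point. The primary outcome definition is itself set out here, with a formula, and it conflicts with the abstract; the sample size is built on it.

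**Conclusion.** The point holds: the primary comparison is not fixed. The visit and the all-or-any rule are unstated, the abstract and the Primary outcomes section disagree on whether there is one outcome or several, and one unadjusted threshold covers both visits.

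The size that needs least assumption is a false-positive chance of about 7–9% in place of 5%, for one composite at two visits with assumed correlation 0.9–0.5. The larger figures (29–34%, or 40% if independent) hold only if the five tests are taken as separate primaries. The 80% power is not shown to be wrong. It is correct for an endpoint with recovery rates of 0.25 and 0.64, but the document does not say which endpoint that is, and those rates name no visit and leave out vHIT.

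**What to change.** 1. In Primary outcomes, name one patient-level composite at one visit, for example week 8. State whether recovery means all baseline-abnormal tests normal or any one normal, and choose the rule that matches how 0.25 and 0.64 were derived. Requiring all tests to be normal is one reasonable choice, not the only one.
2. State that this endpoint is analysed in the ITT set and tested once at two-sided 5%. Make the other visit, the individual tests and the per-protocol analysis supportive, reported with confidence intervals.
3. Because Time points repeats only tests with previous abnormal results, say how a test that was normal at week 4 counts at week 8.
4. Align the abstract with the Primary outcomes section.
5. In the sample size section, either state that the 80% power rests on rates from a battery without vHIT, or recompute the rates from the preliminary data for the chosen endpoint and visit.

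**Cost.** If the existing rates fit the chosen endpoint, this is wording only and 30 per arm stands. Week 4 and single-test results could then no longer carry the claim. A strict all-normal rule may lower power if 0.25 and 0.64 were per-test rates (71% or 36% with three or four abnormal tests, under the assumptions in step 4).

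If several comparisons must be able to carry the claim, Bonferroni with Fisher's test and 0.25 vs 0.64 for every comparison needs, before dropout, 35 per arm for two visits (0.05/2 = 0.025) or 47 per arm for five tests at two visits (0.05/10 = 0.005).

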#### Secondary outcomes

Secondary outcomes include the change of subjective evaluations in vestibular, tinnitus, and hearing assessments:
Change of DHI and VAS-V, VAS-T scores: change of DHI and VAS-V scores from baseline at 1-, 2-, 4-, and 8-week follow-up.Change of PTA: change of average of PTA from baseline at 1-, 2-, 4-, and 8-week follow-up; in this study, we define a 10-dB PTA criterion as clinically significant difference based on a previous RCT [9].Safety: rates of study-related adverse events (AEs), such as short-term systemic use of glucocorticoids related SAEs and AEs, and intratympanic injection-related AEs.

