### Interventions and comparisons

Once a participant is randomized, the treatment procedure starts immediately (Table 1). The participants in group 1 will receive oral prednisone 1 mg/kg/day (maximum daily dosage is no more than 60 mg) for 7 days, followed by a 7-day taper (Table 1). The patients are advised to take the medicine in 30 min before every breakfast, and not to divide the doses. The participants in group 2 will receive 7 intratympanic 40 mg/ml methylprednisolone injections in 14 days, one injection every other day.

**Table 1 Tab1:** Glucocorticoid therapy protocol in each group

	Drug	Protocol
Group 1	Pred.	Glucocorticoid therapy: d1–d7: Oral Pred. 1 mg/kg/d (maximum daily dosage is no more than 60 mg) d8–d9: Oral Pred. 10 mg less than d7 d10–d11: Oral Pred. 10 mg less than d9 d12: Oral Pred. 10 mg less than d11 d13: Oral Pred. 10 mg less than d12 d14: Oral Pred. 10 mg less than d13^a^
Group 2	Met.	Glucocorticoid therapy: One intratympanic injection of 40 mg/ml Met. at d1, d3, d5, d7, d9, d11, and d13;^b^

Pred. prednisone, Met. methylprednisolone, d. day

^a^If the patient’s weight is less than 50 kg, the administration will be stopped after the day with < 10 mg prednisone administered, for example, a patient weighs 45 kg will stop receiving glucocorticoids at the 13th day

^b^One day early or late of injection is allowed for practicality

The otolaryngologists in charge of the injection work are asked to inject at the posterior superior quadrant and fulfill the tympanic cavity using operating microscopes, after lidocaine spray anesthesia. Patients will be asked to keep supine position with the affected ear slightly up to 30° and avoid swallow during injection and in 30 min after the injection. The drug for injection is methylprednisolone sodium succinate for injection by Pfizer Manufacturing Belgium NV.

Of all the participants, the length of treatment would be extended for another week if the change in hearing threshold (average dB in PTA) is less than 10 dB, or average of PTA is worse than 55 dB in the patient’s affected ear, under the participant’s agreement. The salvage treatment regimen is 3 injections of 40 mg/ml methylprednisolone every other day. Records and effects of the salvage treatments will be reported in the study results and evaluated according to both intention-to-treat (ITT) and per-protocol analyses. For those with severe vertigo attacks, drugs for symptom control like mannitol or diazepam can be used temporarily.

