### Adverse events

Any untoward medical occurrences with unfavorable symptoms in the participants are defined as adverse events (AEs). AE is not necessarily to have a causal relationship with the treatment. If the AEs are life-threatening, result in death, persistent, and significant disability or incapacity, or make the participants’ hospitalization, we define them as serious adverse events (SAEs). The investigators will routinely ask the patients if there have been any unexpected symptoms. Study-related and non-study-related AEs will be recorded in the patient’s clinical history by doctors in clinics and then reported to a trial investigator ([name]). Participants experiencing AEs will be followed up until the end of the events or the end of the trial. Any SAEs during this trial will be reported to the trial steering committee (TSC) and Adverse Drug Reaction Administration (ADRA) of the Eye & ENT Hospital of Fudan University within 48 h at learning of the event.

We list some possible study-related AEs here:
Short-term systemic use of glucocorticoids related SAEs: fracture, sepsis, and venous thromboembolism [29];Short-term systemic use of glucocorticoids related AEs: blood glucose problem, appetite change, sleep change, weight change; andIntratympanic injection-related AEs: ear pain, ear infection, tympanic membrane perforation, and worse vertigo after injection.

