### Blinding

We decide not to set blindness of the interventions to patients and doctors, because that setting blindness to patients and doctors will need placebo injections to some of the participants, which may bring unnecessary pain and tympanic membrane perforation risk to the patients. The specialists in test rooms and statistical analysts will be kept blinded during the trial until the statistical analyses are done.

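### The named safety outcome counts only study-related adverse events in an open-label trial, so an arm difference may partly reflect attribution rather than event rates

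*Protocol article*

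**What the plan says.** The Secondary outcomes section of the protocol article limits the safety outcome to "rates of study-related adverse events (AEs"). In full, the item reads: "Safety: rates of study-related adverse events (AEs), such as short-term systemic use of glucocorticoids related SAEs and AEs, and intratympanic injection-related AEs". No rate of all adverse events or of all serious adverse events is named as an outcome.

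The Adverse events section is broader. On the definition it says "AE is not necessarily to have a causal relationship with the treatment". On elicitation, "The investigators will routinely ask the patients if there have been any unexpected symptoms". On recording, "Study-related and non-study-related AEs will be recorded in the patient’s clinical history by doctors in clinics", after which the events go to a trial investigator. The section then gives examples under the words "We list some possible study-related AEs here". Changes in blood glucose, appetite, sleep and weight stand under systemic glucocorticoids. Ear pain, ear infection, eardrum perforation and a worsening of vertigo that follows an injection stand under the intratympanic route.

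The Blinding section says "We decide not to set blindness of the interventions to patients and doctors". Only the test-room specialists and the statistical analysts are blinded, and the Adverse events section gives neither group a part in assessing adverse events.

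**The concern.** An outcome limited to related events is the product of two things: how often the event happens, and how often it is called related. Randomisation protects the comparison of the first. Only blinding, or a rule applied identically in both arms, protects the second, and the article describes neither for relatedness.

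The example categories are worded by route. Someone who knows the allocation could more readily call a sleep change related in a patient taking oral prednisone, and an ear symptom related in a patient receiving injections. Worsening vertigo shows the difficulty most clearly. Every participant enters with vertigo or imbalance (Participants), so it can worsen in either arm, yet the listed form of the event requires an injection.

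The comparison will be read closely. The Background section gives the sparing of systemic steroid side effects as one of two reasons for thinking the intratympanic route superior. A safety difference in that direction would seem to confirm the rationale, and a reader could not tell how much of it was classification.

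**Working it through.** **The passages side by side**

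| Question | Protocol article | Section |
|---|---|---|
| What counts as an adverse event? | Any untoward occurrence; causality not required | Adverse events |
| What is recorded? | Related and unrelated events | Adverse events |
| How is it elicited? | A routine open question, not differentiated by arm | Adverse events |
| What is the named outcome? | Study-related events only | Secondary outcomes |
| Who is blinded? | Test-room specialists and analysts | Blinding |
| Who judges relatedness, and by what rule? | Not stated | – |

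Definition and collection do not depend on attribution. The named outcome does.

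**Is there a figure in the plan to reproduce?** No. The article gives no adverse event rate and no attribution rate, so what follows shows the mechanism and does not estimate the bias.

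**Illustration**

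- From the article: n = 36 per arm (Sample size and statistical methods), with relative risks planned for dichotomous variables.
- Assumed: a single event type with the same true rate r in both arms; a share a of the oral cases and a share b of the intratympanic cases called related; no dropout; a two-sided Fisher's exact test at 0.05, enumerated in full. The article plans chi-squared tests for between-group dichotomous outcomes, so the probabilities are indicative.

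The apparent relative risk is (r × a)/(r × b) = a/b, whatever r is. The true relative risk is 1.

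With a = 0.8 and b = 0.2, the apparent relative risk is 0.8/0.2 = 4. Expected counts are 36 × r × 0.8 and 36 × r × 0.2.

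| True rate r, both arms | Expected related, oral | Expected related, intratympanic | Chance of p<0.05, related events only | Chance of p<0.05, all events |
|---|---|---|---|---|
| 0.10 | 2.88 | 0.72 | 0.034 | 0.014 |
| 0.20 | 5.76 | 1.44 | 0.224 | 0.026 |
| 0.30 | 8.64 | 2.16 | 0.462 | 0.028 |
| 0.40 | 11.52 | 2.88 | 0.658 | 0.026 |

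Range over the attribution assumption:

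- At 90% against 10%, the apparent relative risk is 0.9/0.1 = 9, and the chances at the same four rates are 0.073, 0.451, 0.779 and 0.932.
- At 60% against 40%, the apparent relative risk is 0.6/0.4 = 1.5.
- With equal attribution it is 1 and the problem vanishes.

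The direction could also differ between event types, so the net effect on a combined rate of related events could favour either arm or partly cancel.

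Neither the sample size nor the power of the primary comparison is affected.

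**The case against.** The strongest reply is that collection is sound and the rest is tabulation. All events are recorded whatever their cause, patients in both arms are asked the same open question, and every serious event goes to the steering committee and the hospital's drug-reaction body within 48 hours. A journal article usually leaves adverse event tables to a fuller document, and nothing in this one forbids a table of all events. Vertigo is also measured without attribution, by DHI and VAS-V in both arms. No safety hypothesis is powered.

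Much of that stands, and it keeps the point small. It does not remove it, because the article is not silent on the safety outcome: it names one, and the one it names is conditional on relatedness.

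A reader might infer more than the text supports:

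- *That unblinded doctors make the attribution.* The article says that clinic doctors record events and pass them to a trial investigator. It does not say who assigns relatedness. What can be said is that no blinded judgement is described.
- *That the arms are compared on different events.* The route lists are examples, not closed sets, and no section confines an event type to one arm. This is a risk of the definition and not a stated rule.
- *That sleep or glucose change will be called unrelated in the intratympanic arm.* Both arms receive a glucocorticoid, and nothing in the article predicts how such events would be judged.
- *That salvage injections spoil the oral arm's safety count.* The article states "The salvage treatment regimen is 3 injections of 40 mg/ml methylprednisolone every other day" and opens this to eligible participants of both arms. Counting later events in the randomised arm is intention-to-treat, so this is no fault.

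**Conclusion.** The concern holds as a weakness in the outcome definition. The compared safety rate is restricted to study-related events, in a trial where patients and doctors are unblinded and no blinded judgement of relatedness is described, while all events are recorded regardless of cause. A between-arm difference in that rate may therefore partly reflect attribution.

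Its size cannot be derived from the article. The relative risk of 4 and the chances of roughly 0.03 to 0.66 rest wholly on the assumed 80% and 20% attribution and on assumed true rates of 0.10 to 0.40; they show what the definition permits, not what will happen. The article does not show that differential attribution will occur. The point is minor: it touches a secondary outcome and is settled by rewording.

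**What to change.** Reword the safety item under Secondary outcomes so that the compared outcome is the rate of all adverse events and the rate of all serious adverse events by randomised arm, regardless of relatedness. Classify event types identically in both arms; for example, count worsening vertigo as such, whether or not it followed an injection. Report the study-related subset as a supplementary display.

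This needs no extra visit, test or participant, because both kinds of event are already recorded. The one cost is a slightly noisier rate, since events with no link to treatment are included and can dilute a real difference. The supplementary display keeps the narrower view available.
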